## Abstract

**Background:**

Breast cancer is the most common cancer diagnosed in women worldwide. In developed countries, 80–90% of women will survive five years after diagnosis but the transition from hospital-based care to health self-management and self-efficacy can be difficult. Text messaging programs offer a simple and proven way to provide support to people with chronic diseases. This study aims to test the effectiveness of a text message support program at improving women’s health self-efficacy, and physical and mental health outcomes after breast cancer treatments compared to usual care at 6-months and to understand the barriers and enablers to widespread implementation.

**Methods:**

Single-blind randomised control trial (RCT; *N* = 160) comparing a text message support intervention to usual care in women with breast cancer (recruited from a large tertiary referral hospital in Sydney, Australia). The intervention group will receive a six-month text message support program, which consists of semi-personalised, supportive, lifestyle-focused text messages (4 messages/week) in addition to usual care. The control group will receive usual care without the text message program. Outcomes will be assessed at 6-months. The primary outcome is change in self-efficacy for managing chronic disease. Secondary outcomes include change in clinical outcomes (body mass index), lifestyle outcomes (physical activity levels, dietary behaviours), mood (depression and anxiety scales), quality of life, satisfaction with, and usefulness of the intervention. Analyses will be performed on the principle of intention-to-treat to examine differences between intervention and control groups.

**Discussion:**

This study will test if a scalable and cost-effective text-messaging intervention is effective at improving women’s health self-efficacy, as well as physical and mental health outcomes. Moreover, this study will provide essential preliminary data to bolster a large multicentre RCT to helpsupport breast cancer survivors throughout recovery and beyond.

**Trial registration:**

Australia New Zealand Clinical Trials Registry (ANZCTR) number ACTRN12618002020268, 17 December 2018

## Background

Breast cancer is the most common cancer diagnosed in women worldwide [1]. Due to improvements in diagnostics and treatments in developed countries, 80–90% of women survive at least 5 years after their initial diagnosis [2]. During treatments, patients typically visit their doctors weekly and then gradually reduce to annual visits [3]. During this transition from hospital-based care to health self-management, breast cancer survivors are encouraged to exercise, maintain a healthy diet and weight [4], and, in the majority of cases, adhere to endocrine treatments [5] to reduce the risk of breast cancer recurrence. Many survivors find this transition physically and mentally difficult due to reduced interaction with, and psychological support from, medical professionals [6] and/or ongoing treatment side effects [5]. Therefore, simple and cost-effective strategies are needed to support breast cancer survivors during their recovery and beyond.

Self-efficacy is a person’s confidence with successfully completing a task. Self-efficacy can be improved through 1) learning information 2) motivating goal setting and self-evaluation and 3) achieving goals. Moreover, self-efficacy is domain specific, indicating that people can improve self-efficacy for one task, such as medications adherence, but it will not improve self-efficacy for another task, such as engaging in physical activity [7, 8]. Research shows that educating people about health self-management has been found to improve self-efficacy [7, 9–12], reduce inaccurate illness perceptions [9], drive behaviour change and improve health outcomes [7, 9–12]. However, education programs commonly involve in-person or phone-based counselling, which are labour and cost intensive [13, 14].

Mobile health (mHealth) is the use of mobile technologies, such as mobile phones and applications, to support healthcare delivery [15]. mHealth interventions are cost-saving compared to traditional education programs [16, 17] and align well with self-efficacy principles by providing encouragement to achieve health goals, improving health self-management skills through education and goal setting, and tracking progress and accomplishments [18, 19]. However, most studies target improvements in only one self-efficacy domain. For example, a pre-post study using an interactive weight-loss app found that improvements in eating self-efficacy was related to weight-loss in overweight/obese endometrial and breast cancer survivors [20]. Another study tested three apps, which used self-guided cognitive behavioural therapy to improve mental health, emotional self-awareness and coping self-efficacy compared to usual care and found that coping-self efficacy mediated improvements in depression scores for people who accessed a national mental health organisation website [21]. However, it is unclear if mHealth interventions that target multiple self-efficacy domains can promote improvements in various health outcomes simultaneously.

Text messages are currently the widest-reaching mHealth intervention, as they do not require the internet for delivery [22, 23]. Globally, there are more than 5 billion unique mobile phone users from urban and rural communities [23], and these users send more than 18 billion text messages per day [24]. Text-messaging has, therefore, been targeted as a simple tool for providing people with health information [22]. Recently, the Tobacco, Exercise and Diet Messages (TEXTME) randomised controlled trial (RCT) tested a lifestyle-focused text message intervention (4 messages per week for 6 months), which provided health advice, motivational reminders and support to change lifestyle behaviours compared to usual care for people with coronary heart disease who had recently been hospitalised. At six-months, results showed the TEXTME program effective for promoting healthy behaviours and improving clinical outcomes, such as low-density lipoprotein (LDL)-cholesterol, body mass index (BMI), rates of healthy eating and smoking cessation compared to usual care [25, 26]. Moreover, participants found the TEXTME program useful (91%) and motivating (77%) during their transition to health self-management [27]. For women with breast cancer, text message programs have been shown to help reduce weight, improve exercise frequency, adherence to endocrine therapies [28] and improve motivation to achieve health goals [29]. Although these studies used strategies that are known to improve self-efficacy, such as providing education and motivational information [7], they did not specifically investigate self-reported changes in self-efficacy.

The current study aims to improve self-efficacy in multiple domains related to chronic disease risk factors (physical activity, nutrition, social and emotional well-being, medication adherence, breast cancer knowledge) by providing educational, motivational and supportive information via text message during the difficult transition from hospital-based care. Therefore, this study aims to test the effectiveness of a six-month text message program [9] in addition to usual care and test its efficacy in improving women’s self-efficacy for managing chronic disease after breast cancer treatments compared to usual care alone. We also aim to determine if the text message program can improve anxiety, depression, BMI, healthy eating behaviours, physical activity and quality of life, and if self-efficacy mediates these improvements. Finally, this study aims to investigate the barriers and enablers to implementing such a program with women recovering from breast cancer treatments.

## Methods

### Study design

Single-blind RCT with a six-month follow-up comparing a text message support intervention to usual care in a population of women with breast cancer (Fig. 1). Written and informed consent will be obtained from all participants, and the study will follow the Consolidated Standards of Reporting Trials guidelines [30]. Clinical, behavioural and quality of life data will be collected at face-to-face assessments. To maintain blinding, randomisation will occur after the assessment via computer, which delivers an automated text message to participants regarding study groups but does not reveal allocation to the research assistant. Primary ethics approval has been received from the Western Sydney Local Health District Human Ethics Research Committee (AU RED HREC/18/WMEAD/281).

**Fig. 1 Fig1:**
[figure not shown]
Study flow diagram. Eligible participants who agree to participate (i.e. sign consent form) are randomised to the intervention (text message program) or control (usual care) by a computerised programme. Baseline, follow-up and focus group assessments are performed

### Randomisation and blinding

After the baseline assessment, participants will be randomised to either usual care (control) or the text message intervention group in a uniform 1:1 (control:intervention) allocation ratio, using a secured central computer-based randomisation service. For each participant, the computer system automatically produces a study identification number, which will be used on all study documents. Within 7 days after the enrolment visit, the computer system automatically starts sending the text message program to the participant. Therefore, the researcher conducting baseline and six-month face-to-face assessments remains blinded to treatment allocation. As an additional precaution and for safety purposes, there will be an independent, unblinded researcher monitoring all incoming text messages.

To validate the self-reported physical activity questionnaire, a subset (32/160) of participants, will be randomly assigned to wear a small (matchbox sized) accelerometer for 7 days [31] at baseline and follow-up and return it to a member of the research team.

### Study population

Patients will be eligible to participate if they are female; > 18 years old; diagnosed with breast cancer; have completed breast cancer treatments (surgery, and/or chemotherapy and/or radiation therapy) within the past 18 months (although can still be on endocrine treatment); own an operational mobile phone capable of sending and receiving text messages; and, provide written informed consent. Patients will be excluded if they: are already participating in a text message-based study; have been diagnosed with distant metastatic breast cancer or cannot comply with study requirements (i.e., does not want to return for a follow-up visit, does not want to wear accelerometer). For those people who are ineligible or decline to participate, we will keep a ‘screening log’ of basic demographic information and reasons for non-participation.

### Study groups

*The usual care (control) group* will continue to receive usual care from their assigned health professionals, including support from breast care nurses and other allied health professionals. Participants in the usual care group will receive an initial text message welcoming them to the study, but they will not receive the text message support program. The control group will also receive a text message reminder approximately six-months after their enrolment, notifying them that they will be contacted to schedule their six-month follow-up visit. Participants in the control group will be offered the opportunity to receive the intervention at the end of the study if they wish.

*The intervention group (intervention)* will receive a text message support program in addition to usual care, where they will receive four messages per week at random times and days for 6 months. Participants will be informed that this is a one-way message program and not to reply. However, in case of replies we have a successful system (software program and a centrally located health counsellor with a clinical background) for monitoring all reply messages for safety. The messages will be semi-personalised, where some contain the participant’s preferred name and are tailored for individual circumstances and preferences (e.g., taking endocrine treatments or not). The messages will be sent from our team’s purpose-built and centralised web-based platform that provides simple registration and automated message delivery [32].

The message program content and structure was developed according to our previously published model [33], which involves a multiphase process of identifying breast cancer clinicians and survivors, hosting interactive workshops, and developing relevant and practical content, grounded in evidence-based guidelines and behaviour change theories and women’s lived experiences with breast cancer survivorship. The text message content (max. 100–250 characters) will provide support through education, practical health advice for specific and manageable behaviour change, motivational reminders for setting simple goals, and self-monitoring of goal achievement related to self-efficacy for managing chronic disease. Also, the messages strive to reinforce the initial advice and counselling that the patients received in the hospital. We used a patient-centred approach to develop messages relevant to women with breast cancer and common challenges of breast cancer survivorship [34]. The following message themes emerged: 1) general breast cancer information; 2) physical activity and nutrition; 3) medication adherence and symptom management; and, 4) emotional and social support and well-being.

Each week, messages will be selected from the message bank by the software system based on pre-specified algorithms that ensure that participants are receiving the correct messages (intervention vs control) and that the intervention group receives a variety across the four message themes. Both intervention and control groups will receive a welcome message at the beginning of the study and a concluding message at the end of the 6 months. All participants will receive training on how to read, reply, save and delete text messages. All participants will also be provided with the research personnel’s contact details and will be contacted at least once during the intervention period to facilitate the six-month follow-up interview. A researcher will manage a study mobile phone, and a record will be kept of any incoming messages from participants and all out-going replies from the study health counsellor throughout the study. Any analyses of these incoming text messages will be performed at the group level, except for reporting examples of individual quotes, which will be anonymised to protect the participant’s identity. Participants from either group can withdraw from the study at any time without giving a reason by replying ‘STOP’ to any of the messages or contacting a member of the research team, which will activate a process of review and withdrawal from the study. If a participant withdraws, no further information will be collected.

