### Sample size and statistical analysis plan

A mean difference of 1 unit on the average score between patients in the intervention and control groups on the Self-Efficacy for Managing Chronic Disease Scale (6 items) would be a clinically meaningful improvement. A standard deviation of 2.05 for the Self-Efficacy for Managing Chronic Disease Scale (6 items) score (an average of the six items) was published in a similar cancer population [45]. With a 20% drop out rate, 80% power and type I error of 5%, a total of 160 patients will be needed, with 80 patients in each arm (intervention: control).

All analyses will be performed according to the intention-to-treat principle by a blinded statistician. Continuous variables will be summarised as means and corresponding 95% confidence intervals (CIs), or if the distribution is skewed, as medians and interquartile intervals. Categorical variables will be summarised as frequencies and percentages. Primary outcome will be compared between the intervention and the control groups at 6-months using analysis of covariance (ANCOVA), adjusting for the baseline measure of the primary outcome. Similarly, for each of the secondary outcomes, ANCOVA, adjusting for the baseline value of the outcome, will be used to compare between the groups at 6-months. We will also investigate if changes in secondary outcomes are mediated by self-efficacy scores. A significance level of 0.05 will be used. All analyses will be undertaken using SAS 9.4 for Windows.

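### A STOP reply to any message ends study follow-up as well as the messages, so avoidable loss of six-month outcomes is likely to fall mainly on the intervention arm and weakens the intention-to-treat comparison

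*Protocol article*

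**What the plan says.** The exit route is set out in the Study groups section of the protocol article: "Participants from either group can withdraw from the study at any time without giving a reason by replying ‘STOP’ to any of the messages", or by contacting the research team. The consequence follows at once: "which will activate a process of review and withdrawal from the study. If a participant withdraws, no further information will be collected". No intermediate status is described in which the messages cease and follow-up continues.

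The same section sets the exposure to messages. In the intervention group "they will receive four messages per week at random times and days for 6 months". The control group "will receive an initial text message welcoming them to the study, but they will not receive the text message support program"; besides the welcome it gets a reminder at about six months and a concluding message.

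Table 1 (Data collection) schedules the primary self-efficacy scale at baseline and six months only. The section Sample size and statistical analysis plan states "All analyses will be performed according to the intention-to-treat principle by a blinded statistician", with a baseline-adjusted ANCOVA at six months as the primary comparison.

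**The concern.** Stopping the allocated treatment and leaving the study are different events, and an intention-to-treat comparison depends on keeping them apart: a woman who gives up the programme should still contribute her six-month score to her own arm. Here the reply that ends the messages also ends data collection, and with a single post-baseline assessment nothing can stand in for the lost value.

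The rule is written alike for both arms but cannot operate alike. For most of follow-up a control woman has only the welcome message to answer, because her other two messages arrive at about six months. An intervention woman is prompted four times a week and is the only one with a programme she might want to end. At stake is the comparability of the women who reach the primary analysis. There is a side effect too: the acceptability survey is completed by intervention women at the six-month visit, so those who stopped would not answer it.

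**Working it through.** **1. What happens to a woman who sends STOP**

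| Step | Source | Result |
|---|---|---|
| She replies STOP to a message | Study groups | Review, then withdrawal from the study |
| She is withdrawn | Study groups | No further data |
| Next scheduled primary measurement | Table 1 | Six months, not collected |
| Primary analysis | Sample size and statistical analysis plan | No six-month score to enter |

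**2. Exposure to the trigger.** Taking six months as 26 weeks, the intervention arm gets 4 × 26 = 104 programme messages, plus the welcome and concluding messages. Control gets a welcome, a reminder and a concluding message, which makes 3.

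**3. The plan's own figure.** Inputs are a difference of 1, SD 2.05, 80% power and 5% type I error (taken as two-sided).

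- n per arm = 2 × [2.05 × (1.960 + 0.842) / 1]² = 66.
- 66 × 1.2 = 79.2, rounded up to 80 per arm, or 160 in all, as stated.
- A 20% loss is 32 of 160 women and leaves 64 per arm if it is even.

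**4. Is lost power the problem?** Power = Φ(1 / [2.05 × √(1/n₁ + 1/n₀)] − 1.96). The split of the 32 losses is assumed.

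| Losses, intervention / control | Analysed | Power |
|---|---|---|
| 16 / 16 | 64 / 64 | 78.8% |
| 24 / 8 | 56 / 72 | 78.2% |
| 32 / 0 | 48 / 80 | 76.2% |

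Even a wholly one-sided loss costs under 3 points. The issue is bias, not power.

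**5. Possible bias.** Let p be the share of the intervention arm lost through STOP, and g the amount by which their six-month mean would lie below that of the women who continue (mean m). The mean of the whole arm is (1 − p)m + p(m − g) = m − pg, so analysing only those observed overstates the arm mean by p × g. Neither p nor g is in the documents; both are assumptions.

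| Stoppers among 80 (p) | g = 1 unit | g = 2 units |
|---|---|---|
| 4 (5%) | 0.05 | 0.10 |
| 8 (10%) | 0.10 | 0.20 |
| 16 (20%) | 0.20 | 0.40 |

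If stoppers would have scored higher, g is negative and the bias runs against the programme.

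**6. Effect of baseline adjustment.** Suppose stoppers were already g lower at baseline, with equal SDs and a baseline-to-six-month correlation r. ANCOVA then leaves p × g × (1 − r). With r assumed between 0.3 and 0.7, a bias of 0.10 falls to between 0.07 and 0.03, and 0.40 to between 0.28 and 0.12. If the deficit is unrelated to baseline, the bias is not reduced.

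**7. After the change.** A woman who stops the messages but is assessed at six months is not lost, so p by this route is 0 and so is the bias.

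**The case against.** - **Either arm can use STOP.** A reader might infer that only intervention women who disliked the programme are lost, and that the result must favour the programme. The documents support neither. They give no STOP rate, no split by arm and no reasons. A woman may stop because she feels confident and needs no support, and a control woman may leave because she was not given the programme. What survives is that the imbalance in exposure makes loss mainly from the intervention arm likely; the sign of any bias stays open.
- **A review comes first.** STOP activates "which will activate a process of review and withdrawal from the study", and in practice the review might separate the two wishes. Its detail may sit in the full protocol, which is not shown. The text also does not say that a woman who asks the team to end only the messages must be withdrawn. The merging is thus established for the STOP reply alone, but there withdrawal is the only outcome given.
- **An unseen analysis plan may deal with missing data.** It may, and its absence here is no fault. It can model the gap but cannot recover outcomes that the protocol says will not be collected.
- **Women have a right to withdraw.** They do, and ending collection on a real withdrawal is not an error. The point concerns only counting a message opt-out as one.
- **The bias could be turned into a false-positive rate.** That is tempting, but such a figure would depend on how stopping relates to baseline score and on the baseline-to-follow-up correlation, neither of which is documented. A rate from an unadjusted comparison would not describe the planned ANCOVA and could err either way, so none is given.
- **A contradiction with the advice not to reply.** The section says "Participants will be informed that this is a one-way message program and not to reply", and a reader might set this against the STOP route. A one-way programme with a keyword exit is coherent: the section goes on to describe monitoring of replies and says all participants are trained to reply. This is no finding.

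**Conclusion.** The point holds as a badly fixed conduct rule. A STOP reply to any message removes a woman from follow-up, no route is described for stopping the messages alone, and this works against the intention-to-treat analysis that the plan states. That the loss will fall mainly on the intervention arm is an inference, though a strong one, from about 104 programme messages against about three administrative ones. Bias towards the programme is plausible if stoppers do worse, but it is not shown. On assumed inputs it runs from about 0.10 units (10% stopping, 1 unit lower) to about 0.40 units (20% stopping, 2 units lower), or 10% to 40% of the 1-unit target before baseline adjustment. The upper figure is an extreme case, since it makes the whole 20% allowance in that arm consist of STOP replies. Loss of power is minor. The change is still worth making because it is cheap and a missed six-month score cannot be obtained afterwards.

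**What to change.** Amend the Study groups section, the consent form and the procedure for handling STOP replies so that, in both arms:

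- STOP ends the messages only.
- The woman is still invited to the planned six-month visit and is analysed in her allocated arm.
- Data collection ends only if she explicitly withdraws from follow-up.
- Data already collected are kept, subject to her consent.

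The cost is a small amendment and a brief check of her wishes within the review step that the protocol already describes. The independent unblinded researcher who monitors incoming texts could make that check, which would keep the assessor blinded. No extra patients or scheduled visits are needed.
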